#### For secondary outcomes and aims

For clinical secondary outcomes (secondary aim 1), t-tests or Mann–Whitney will be used for continuous variables (according to normality of data distribution). A Kaplan-Meier curve will be constructed for each group for ‘time to resolution’ and ‘time to next exacerbation’ as done previously [53]. For secondary aim 2 (factors that predict response to antibiotics), univariate analysis will be used to examine the biological factors listed above. Factors that have a *P-*value < 0.2 will be included in a logistic regression model. Potential interactions (for example, virus with bacteria) will be examined in the model. Descriptive data will be used for secondary aim 3 (point prevalence of respiratory pathogens).

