### End points

Participation is complete when the child’s clinical state returns to baseline and the ‘time to next exacerbation’ has been obtained. Other exit points are if the child is clinically worse prior to day 14 or intolerance to the trial medications requiring withdrawal from the study (as determined by the treating clinician).

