### Outcome measures

#### Primary outcome

The primary outcome is the proportion of children whose exacerbations have resolved by day 14. Exacerbations will be considered resolved when symptoms and signs are the same as the baseline state. Children who are withdrawn from the study or receive additional antibiotic treatment will be categorised as non-resolved.

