#### Secondary clinical outcomes

The main secondary outcome is the PC-QOL score. Other outcomes are the time to next exacerbation; requirement for hospitalisation; duration of exacerbation (persistence of symptoms till ‘return to baseline state’) and FEV_1_% predicted.

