### Sample size

We plan to enrol 189 children (63 per arm), providing 84% power (α = 0.0245, two-sided) to detect a halving of the number of children in the active arm achieving resolution by day 14 (that is, azithromycin or amoxicillin-clavulanic acid: 60% resolved by day 14, compared with placebo: 30% resolved). This is a conservative estimate when compared with our prospective data of persistent symptoms in 24% of children based on the same diary card [50]. As the primary outcome will be obtained in all enrolled children, a drop-out has not been factored in for the intention-to-treat analysis. With 20% drop-out rate, data from 153 children (51 per arm) for ‘per protocol’ analysis provides a study power of 75%. Both treatment arms are compared with the same placebo arm. While the maximum efficiency is attained by allocating more children to the placebo arm (that is, using an allocation ratio of 1:1:√2), we chose to use a 1:1:1 allocation due to ethical concerns of deviating from standard care in respiratory centres.

In the main secondary outcome (PC-QOL), based on a between-group difference of 0.9 (minimum important difference [42]) (SD 0.9), our sample size provides power of 100% (α = 0.05) for data from at least 147 children (that is, assuming at least 80% retention of the 189 children enrolled). For secondary aim 2 (exploring factors that predict response to antibiotics), we will be examining eight main factors and thus a sample size of 147 exceeds the recommended minimum (n = 10 per factor) [51]. The eight factors are smoking, age, underlying aetiology, detection of virus (any versus none, then single versus multiple viruses), presence of azithromycin resistance and blood markers (IL-6, IL-10, IP-10 levels).

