### Statistical analysis and reporting

Data will be reported and presented in accordance with the updated CONSORT criteria [52]. Children will be analysed according to allocation status (regardless of subsequent management). An interim analysis is planned and a data safety and monitoring committee will determine if the study should be ceased should superiority of any antibiotic be identified after 50% of sample size is achieved.

For our primary aim, the main effects of the interventions will be determined by comparing the primary outcome (resolution of exacerbation) between groups ((azithromycin versus placebo) and (amoxicillin-clavulanic acid versus placebo)). Children who exit the study as clinically worse or drop-outs prior to the end point will be considered non-resolved. Those who exit the study as ‘returned to baseline’ will be considered resolved. Odds ratios will be calculated and, if appropriate, number needed to treat (for benefit) will be expressed. Tests of a treatment arm versus placebo at the end of the study for the primary outcome will be performed at the 2.45% significance level to account for spending some alpha at the interim analysis. Per protocol analysis will be an *a priori* secondary analysis.

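### The time-to-resolution curve does not carry over the non-resolved rule, so censoring early exits in the usual Kaplan-Meier way can put it above the primary day-14 proportion

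*Protocol article*

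**What the plan says.** All references are to the protocol article.

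- **For secondary outcomes and aims:** "A Kaplan-Meier curve will be constructed for each group for" time to resolution and time to next exacerbation, as in an earlier cited study. No censoring rule, between-group test or effect estimate is given for these curves.
- **End points:** "Other exit points are if the child is clinically worse prior to day 14 or intolerance to the trial medications" that require withdrawal. The Discussion section on outcome measures and timeframe also mentions a safety exit at day 7.
- **Primary outcome:** "Children who are withdrawn from the study or receive additional antibiotic treatment will be categorised as non-resolved".
- **Statistical analysis and reporting:** "Children who exit the study as clinically worse or drop-outs prior to the end point will be considered non-resolved". This sentence belongs to the paragraph on the primary aim. The same section says: "Children will be analysed according to allocation status (regardless of subsequent management").
- **Secondary clinical outcomes:** the related outcome is "duration of exacerbation (persistence of symptoms till" return to the baseline state).
- **Sample size:** 63 children per arm, with "azithromycin or amoxicillin-clavulanic acid: 60% resolved by day 14" against 30% on placebo.

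**The concern.** Leaving before resolution is built into this placebo-controlled design. For the primary outcome the article says what such a child counts as: a failure. For the time-to-resolution curve it names a method but does not repeat that rule.

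As usually run, Kaplan-Meier censors a child at last observation. It then spreads that child's weight over those still at risk, on the assumption that they share the same future chance of resolving. For a child taken out because of worsening, that assumption is implausible. The curve would then be read as resolution among children who do not leave, not as resolution among all children allocated.

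Day 14 lies on the curve's time axis and is also the primary time point. A reader may therefore find a resolution percentage on the curve that is higher than the headline figure for the same arm. If exits differ between antibiotic and placebo, the visible gap between the curves is distorted as well.

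**Working it through.** **The plan's own figure.** The article gives no number for the curve. Its only related figure is the power of the primary comparison. The continuity-corrected normal approximation is power = Φ[(d − 1/n − z·SE0)/SE1], with d = 0.30, z = 2.249 (two-sided 0.0245), SE0 = √(0.495/n) and SE1 = √(0.45/n).

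- n = 63: (0.3000 − 0.0159 − 0.1994)/0.0845 = 1.003, giving 84.2% (stated 84%).
- n = 51: (0.3000 − 0.0196 − 0.2216)/0.0939 = 0.626, giving 73.4% (stated 75%).

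Both are within 2 points of the stated figures. Nothing below changes them.

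**Inputs for the curve.** Let r be the share resolved by day 14 with exits counted as failures: 0.60 active and 0.30 placebo (Sample size). Let e be the share leaving unresolved before day 14. The article does not give e, so it is assumed over a range. Two figures in the article do not supply it:

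- The 20% in the Sample size section is a per-protocol drop-out.
- The 23% given intravenous antibiotics in the earlier cohort relates to hospital care that generally began three to five weeks after oral treatment started, which is past day 14.

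**Formula.** Assume constant cause-specific hazards. The chance of neither event by day 14 is 1 − r − e, and a fraction r/(r+e) of the total hazard is resolution. With exits censored, the curve at day 14 reads

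1 − KM = 1 − (1 − r − e)^(r/(r+e)).

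- Active, e = 0.10: 1 − 0.30^0.857 = 0.644
- Placebo, e = 0.10: 1 − 0.60^0.75 = 0.318
- Active, e = 0.20: 1 − 0.20^0.75 = 0.701
- Placebo, e = 0.20: 1 − 0.50^0.60 = 0.340

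| Assumed exits, active / placebo | Active reads | Placebo reads | Difference (true 30.0) |
|---|---|---|---|
| 5% / 5% | 62.1% | 30.9% | 31.2 |
| 10% / 10% | 64.4% | 31.8% | 32.5 |
| 20% / 20% | 70.1% | 34.0% | 36.1 |
| 10% / 30% | 64.4% | 36.8% | 27.6 |
| 10% / 50% | 64.4% | 45.3% | 19.1 |

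Differences are taken before rounding.

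**Scale.** The standard error of one arm's proportion is √(0.24/63) = 6.2 points (active) or √(0.21/63) = 5.8 points (placebo). For the difference it is √(0.45/63) = 8.5 points.

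- At 20% exits per arm, the active curve is off by 10.1/6.2 = 1.6 SE and the placebo curve by 4.0/5.8 = 0.7 SE.
- At 5% per arm, they are off by 2.1/6.2 = 0.3 SE and 0.9/5.8 = 0.2 SE.
- The difference moves by 2.5/8.5 = 0.3 SE at 10%/10%, and by 6.1/8.5 = 0.7 SE at 20%/20%.

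**Sensitivity to timing.** Put all exits at day 7, with a constant resolution hazard. Let x be the share unresolved just before day 7. Then (1 − x)(1 + x − e) = r, and the curve reads 1 − x². For e = 0.20, x = 0.558 (active) and 0.814 (placebo), which read 68.8% and 33.7%. These are close to the constant-hazard values.

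**Check of the alternative.** Cumulative incidence with exit as a competing event gives r/(r+e) × (r+e) = r, that is 60% and 30%. Kaplan-Meier with exits kept at risk to the end of the axis gives the same, because the denominator remains all 63 children.

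**The case against.** The strongest reply is that naming Kaplan-Meier does not force the bias. A Kaplan-Meier curve can hold exited children as unresolved to the end of the axis, and it then matches the primary proportion. The article states no censoring rule, and a condensed article commonly leaves that to the full plan. This stands against a stronger reading that a reader might infer, namely that the method can only censor these children and so contradicts the primary result. The document does not say that. What is left is that the article states a failure rule for the primary outcome and a method for the curve, and the customary use of that method does not follow the rule.

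Second, duration until return to baseline is a different quantity from the binary outcome, and children are analysed whatever their later management. Additional antibiotics make a child non-resolved for the primary outcome but are not listed as an exit point. Such a child can be followed to an observed resolution date with no censoring. This also stands: the two measures may properly differ for these children, provided the choice is stated. It does not cover children whose observation ends at exit.

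Third, the curve is a secondary description with no test attached, and the exit rates are assumed. Both are true, and they limit the weight of the point. In the equal-exit scenarios only 20% per arm moves the between-arm difference by more than half a standard error.

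**Conclusion.** The point holds as an inexpensive improvement to a secondary analysis. If unresolved exits are censored when they leave, the curve overstates resolution in each arm relative to the primary rule. With 5% to 20% exits in both arms, the overstatement is about 2 to 10 points on antibiotic and 1 to 4 points on placebo; at the low end it is negligible. Equal exits widen the apparent difference (31.2 to 36.1 points against 30). Much more frequent exits on placebo narrow it (27.6 points at 10%/30%, 19.1 points at 10%/50%). The order of the arms did not reverse in any scenario tried.

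These sizes rest on assumed exit rates, the planning proportions and constant hazards; moving all exits to day 7 changes little. The primary analysis, its power and the stopping rules are not touched. The documents do not support calling this a contradiction of the primary result. It is a conditional disagreement that one sentence can prevent.

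**What to change.** In the section on secondary outcomes and aims, replace the Kaplan-Meier curve for time to resolution with the cumulative incidence of resolution per arm. Treat unresolved exit before day 14 as the competing event: clinically worse, intolerance, other withdrawal or drop-out. Drop-outs must be included, because the primary rule counts them as non-resolved and the curve will not match at day 14 without them. Equivalently, keep all these children in the risk set as unresolved to the end of the time axis.

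State separately what happens to children who receive additional antibiotics but stay under observation. Either hold them as unresolved, so that the curve matches the primary outcome, or follow them to their observed return to baseline, which fits the duration outcome as defined. Kaplan-Meier can stay for time to next exacerbation.

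The cost is one or two sentences and a standard routine. No new data should be needed: a censored curve would use the same exit times, and the primary outcome already requires exits to be classified. The price is that the reported resolution curves will be somewhat lower.

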Determinants of accelerated lung function decline in adults with bronchiectasis are the frequency of hospitalised exacerbations, increased systemic inflammatory markers and *Pseudomonas aeruginosa* infection [24]. Amongst other factors, increased mortality risk is associated with the degree of lung function impairment [25]. No prospective data exist in children. Our study and a London-based retrospective study found that, with appropriate treatment in specialised centres, lung function improves and can be maintained [18,20]. However, those with poor lung function at diagnosis, although substantially improved, were likely to still have poor lung function five years later [20]. We also found that the only significant predictor of a decline in forced expiratory volume in one second (FEV_1_) was frequency of hospitalised exacerbations [20]. Forced expiratory volume in one second (FEV_1_)% predicted decreased by 1.95% with each previous hospitalised exacerbation [20]. As airway injury in children is superimposed upon the physiological changes involving lung growth and development [26,27], improvement in childhood bronchiectasis may impact favourably upon future adult lung function. Early and effective management of bronchiectasis exacerbations in children may lead to reduced hospitalisations, better quality of life (QOL) and improved future adult lung function.

Antibiotics are one of the key interventions used to treat acute respiratory exacerbations of bronchiectasis [21,28]. However, it is biologically plausible that antibiotics are not useful for treating some respiratory exacerbations triggered by viral infections. Our retrospective study found that 34% of exacerbations were preceded by a viral-like illness [29]. While most respiratory physicians will treat exacerbations intensively (with antibiotics and airway clearance), other doctors do not. Those choosing not to use antibiotics routinely argue that most episodes of exacerbations and cough are caused by viral infections and hence do not require antibiotic therapy. This may be appropriate but viral-bacterial interactions in the airways risk prolonged endobronchial bacterial infection that, with the associated inflammatory cascade, may cause further lung injury [23,30]. Better evidence to guide the management of exacerbations in people with bronchiectasis is needed.

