### Aims of the study

There are two components of BEST; here we present the study protocol of the first phase (BEST-1). The second phase of BEST (BEST-2) will address the question “Is daily azithromycin non-inferior (within 20% margin) to amoxicillin-clavulanic acid in achieving resolution of exacerbations on day 21?” The protocol for BEST-2 will be the subject of a later paper.

This first phase of our proposed national multicentre double-blind double-dummy randomised controlled trial (RCT) is designed to answer our primary questions, as follows. Amongst children with non-CF bronchiectasis, does azithromycin improve the resolution of respiratory exacerbations by day 14 compared with placebo, and does amoxicillin-clavulanic acid improve the resolution of respiratory exacerbations by day 14 compared with placebo?

Our secondary aims are to:

1. determine the effect of azithromycin or amoxicillin-clavulanic acid on the QOL, systemic inflammation, time to next respiratory exacerbation, and duration of exacerbations;

2. explore factors that predict response to antibiotics, including respiratory pathogens (viruses, bacteria, macrolide-resistant bacteria) present in respiratory secretions and blood markers; and

3. describe the point prevalence and diversity of respiratory viruses, *Mycoplasma pneumoniae* and *Chlamydia* species during exacerbations using sensitive molecular detection techniques.

Our study tests the primary hypothesis that both oral azithromycin and amoxicillin-clavulanic acid are superior to placebo in improving the resolution rate of respiratory exacerbations by day 14 in children with non-CF bronchiectasis.

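### The secondary analysis of predictors of antibiotic response names no treatment-by-factor term, so as written it finds factors associated with resolution, and its P<0.2 screen can drop a true modifier

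*Protocol article*

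**What the plan says.** In the protocol article, Aims of the study, secondary aim 2 is to "explore factors that predict response to antibiotics, including respiratory pathogens" and blood markers. The Abstract presents the assessment of predictors of antibiotic response as one of the trial's novel features.

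Sample size justifies this aim by a count of factors: "we will be examining eight main factors and thus a sample size of 147 exceeds the recommended minimum" of 10 children per factor. "The eight factors are smoking, age, underlying aetiology, detection of virus", azithromycin resistance, IL-6, IL-10 and IP-10. Allocation is not on the list. The 147 are described as "assuming at least 80% retention of the 189 children enrolled", so they appear to come from all three arms, placebo included.

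For secondary outcomes and aims gives the method: "univariate analysis will be used to examine the biological factors listed above", those with P<0.2 go into a logistic regression, and "Potential interactions (for example, virus with bacteria) will be examined in the model". No treatment term, treatment-by-factor term or comparison of factor effects between antibiotic and placebo is named for this aim.

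**The concern.** Response to an antibiotic means resolving because of it. Some children resolve without it: the plan itself assumes 30% resolution on placebo. A regression of resolution on patient factors alone cannot separate a child who recovers slowly whatever is given from a child who gains less from antibiotics. Only a comparison of the antibiotic-placebo difference across levels of the factor does that.

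The order of the steps adds a second fault. The screen acts on each factor's pooled association with resolution. A factor that alters antibiotic benefit but leaves average resolution unchanged can be removed before any interaction is examined.

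At stake is the question that the Background raises, that "it is biologically plausible that antibiotics are not useful for treating some respiratory exacerbations triggered by viral infections". Prognostic markers could be reported as predictors of antibiotic response, and the modifier that motivated the aim could be missed.

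**Working it through.** **The plan's own figure.** 8 factors × 10 children = 80, and 147 ≥ 80 (147/8 = 18.4 per factor), so the stated rule is met. It counts eight main effects only. Adding two arm terms and 8 × 2 = 16 arm-by-factor terms would give 26. At the planned rates, overall resolution is (60 + 60 + 30)/3 = 50%, or 73.5 of 147 children; 73.5/8 = 9.2 events per term, against 73.5/26 = 2.8. As a side point, 147/189 = 77.8%, whereas 80% of 189 is 151.

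**Inputs for the check.** From Sample size: 147 children, so 49 per arm under 1:1:1 allocation; 60% resolution on each antibiotic and 30% on placebo. Assumed: one binary factor present in 50% of children, complete data, and the resolution rates by factor level below. In every case the rates average to 60% and 30%. The pooled rate at each level is (2 × antibiotic + placebo)/3.

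| Case | Factor present: antibiotic / placebo | Factor absent: antibiotic / placebo | Pooled: present v absent |
|---|---|---|---|
| A. Prognostic only (benefit 30 points at both levels) | 50 / 20 | 70 / 40 | 40 v 60 |
| B. Strong modifier, cancelling (0 v 60 points) | 50 / 50 | 70 / 10 | 50 v 50 |
| C. Moderate modifier, cancelling (15 v 45 points) | 55 / 40 | 65 / 20 | 50 v 50 |
| D. Moderate modifier, no effect on placebo (15 v 45 points) | 45 / 30 | 75 / 30 | 40 v 60 |

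The screen sees only the last column. A and D are identical there, although A has no modification and D has a threefold difference in benefit. B and C show nothing there, although both are true modifiers.

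**Chance of passing P<0.2 in cases A and D.** With d = 0.20 and 73.5 children per level:
- SE under the null = √(0.5 × 0.5 × 2/73.5) = 0.0825.
- SE under the alternative = √(2 × 0.4 × 0.6/73.5) = 0.0808.
- Pass probability ≈ Φ((0.20 − 1.282 × 0.0825)/0.0808) = Φ(1.17) ≈ 88%.

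If prevalence is 34%, the share of exacerbations that the article says followed a viral-like illness (about 50 v 97 children), case A gives SEs of 0.0869 and 0.0853 and Φ(1.04) ≈ 85%. The result does not hinge on 50% prevalence.

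**Simulation** (3,000 to 20,000 trials per case, 147 children, interaction tested at 0.05 with the two antibiotics pooled; ranges cover likelihood-ratio and Wald tests and separate runs):

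| Case | Passes P<0.2 screen | Interaction test significant |
|---|---|---|
| A | 87% | 4-6% |
| B | 15-18% | 96-97% |
| C | 17-21% | 42-44% |
| D | 87-89% | about 39% |

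**Antibiotic arms only.** Restricting the model to these arms does not help. A purely prognostic factor with a treatment odds ratio of 3.5 at both levels (placebo 40% v 20%, antibiotic 70% v 46.7%) still passes in 85%. A modifier visible only on placebo (antibiotic 60% at both levels, placebo 45% v 15%) is dropped in about 80%.

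**Incomplete specimens.** Specimen collection limits bloods and exacerbation swabs to a subset. That can affect five of the eight factors: virus, azithromycin resistance, IL-6, IL-10 and IP-10. If half the children have data (assumption), interaction power falls to about 67% in case B and about 20% in case C. Azithromycin v placebo alone gives about 90% and 34% with full data, and 57% and 17% with half.

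**The case against.** The strongest reply is that silence is not a choice. The article does not exclude a treatment term, does not name the regression outcome, lists the eight factors in order to justify sample size, and leaves the interactions open-ended. A full analysis plan could supply the missing term. That stands as far as it goes: the absence of a treatment term is inferred from what is listed. A reader might infer that the plan rules out treatment-by-factor terms, and the text does not support that. But the screen and its threshold are stated, and an interaction added at the model stage cannot recover a factor already removed.

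Second, a reader might infer that the screen generally throws away true modifiers. It does not. Cases B and C are built so that the effects cancel; in case D, with the same 45 v 15 point benefit as case C, about 88% pass. In that pattern the screen keeps the factor more often than an interaction test detects it. Keeping it does not help interpretation, however, since case A passes just as often.

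Third, the aim is exploratory and the primary comparisons are untouched. Both are true. That clinicians would withhold or give antibiotics on the strength of this model is conjecture. The 87% is also the chance of passing the univariate screen, not of being reported from the final multivariable model, which was not simulated.

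**Conclusion.** The concern holds in a limited form. The article words the aim as response to antibiotics but specifies a screen and model that, followed as written, identify factors associated with resolution. A purely prognostic factor of 20 points passes the screen in about 87% of trials although there is nothing for an interaction test to find (4-6% flagged). A true modifier may be lost or kept depending on its pattern: about 17% pass when its effects cancel, about 88% when it has no effect on placebo.

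These figures rest on an assumed prevalence of 50%, assumed rates by factor level, and complete data on 147 children. The qualitative conclusion rests on none of these, because the pooled association carries no information on the antibiotic-placebo difference. The point is a correction that should be made to a secondary, exploratory analysis.

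**What to change.** Replace the text for secondary aim 2 along these lines:

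- For each pre-specified factor measured before the first trial dose, fit a logistic model for day-14 resolution in the randomised arms with treatment, factor and treatment-by-factor interaction.
- Do not screen on the main effect.
- Report the antibiotic-placebo difference at each level of the factor with its confidence interval, and the interaction P value.
- For azithromycin resistance, compare azithromycin with placebo. For the other factors, pooling the two antibiotics is an option, with arm-specific estimates also shown because the primary questions are arm-specific.
- Label the results exploratory and unadjusted for multiplicity, and state how many children contribute data to each factor.

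Fitting one factor at a time avoids the 26-term model. If the factor-only model is kept, call it an analysis of factors associated with resolution and do not describe its results as predictors of antibiotic response.

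The cost is wording only; no new patients or data are needed. The downside is low power for moderate modification: about 40-44% with full data, and about 20% if only half the children have specimens (assumption). A non-significant interaction should therefore not be read as evidence that antibiotic benefit is uniform.
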